**Methods/design:**

This non-blinded study will randomize 30 primary care clinics in NC stratified by four PBRNs. We will test dissemination across these practices using a facilitator-led participatory approach to dissemination (FLOW), a novel method of participatory dissemination involving key principles of community-based participatory research, and a more typical “lunch and learn” dissemination method. Specifically, we will use cluster randomization to assign each of the 30 practices to one of three arms: (1) control, no dissemination; (2) traditional dissemination, one didactic session a year and distribution of educational material; and (3) FLOW dissemination. We hypothesize that at the unit of randomization, the clinic, patients in the FLOW dissemination arm will be more likely to share in their treatment decisions compared to patients in the traditional dissemination or control arms. All outcomes will be measured at the level of the clinic. Adoption of the SDM approach will be evaluated by 1) asthma exacerbations, 2) level of patient involvement in the decision making process, and 3) qualitative assessments from patients and providers.

The research question is: What dissemination strategy most effectively increases practice level adoption of a shared decision making approach to asthma management? This study will provide important data to support best practices in dissemination of an evidence-based toolkit and implementation of shared decision making into primary care practices.

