### Description of interventions

This study compares ways to disseminate evidence-based interventions to practices using practice-level dissemination methods. Each dissemination method is designed for practice-wide adoption, and as such, the study will use a practice-level cluster randomized controlled design. The clinics will be stratified based on geographical location within North Carolina. To meet the inclusion criteria, all clinics will have at least 75 patients aged 5–40 with Medicaid coverage and asthma defined by one or more of the following criteria: 1) inpatient visit with an asthma primary diagnosis, 2) emergency department visit with an asthma primary diagnosis, 3) at least four outpatient visits with asthma primary diagnosis and at least two asthma medications, or 4) four asthma medications. Patients with a diagnosis of chronic obstructive pulmonary disease (COPD) will be excluded from the quantitative analyses. All asthma patients at the clinics will be eligible for the intervention, while only the Medicaid patients meeting the above criteria will be included in the exacerbation analysis. Thirty diverse primary care clinics will be recruited from a state-wide pool of eligible clinics geographically accessible to each of the four PBRNs (Figure 1). The first 30 consenting practices will be equally randomized into one of three study arms: (1) facilitator-led participant owned (FLOW) dissemination, (2) traditional dissemination, and (3) control. The cluster randomization of clinics by participating PBRNs (Figure 2) will ensure relatively equal geographical distribution.

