In 2011, Medicaid covered approximately 1.5 million non-elderly individuals in North Carolina with a racial breakdown of 43% White, 35% Black, and 14% Hispanic [23]. Practices accepting Medicaid patients are located in each of North Carolina’s 100 counties, and thus, the population is geographically heterogeneous with both rural and urban representations.

The 30 practices will be recruited by the four PBRNs either from practices within their existing network or practices within an appropriate geographically defined area. Each PBRN has identified practices that meet the study’s inclusion criteria. Individual PBRNs will be responsible for recruiting two or three practices per arm for a total of six or nine practices per PBRN and will be responsible for recruitment and oversight of a practice facilitator. As the lead group, Mecklenburg Area Partnership for Primary Care Research (MAPPR) will be responsible for hosting a centralized training day and ongoing continuing education for all practice facilitators.

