### Analysis

We hypothesize that at the unit of randomization, the clinic, patients in the FLOW approach to dissemination will be more likely to share in their treatment decision compared to patients in the traditional dissemination or usual care arms. Qualitative data will be collected to assist in understanding barriers to implementation, to ensure that patients feel that they are partners in the development of the asthma care plan, and to improve the facilitator-led implementation approach over time.

Also, we hypothesize that clinical outcomes in arm 1 will show greater improvement than arms 2 (traditional) or 3 (control). Bivariate comparisons between study arms will be conducted using chi-square test for proportions and *t*-tests (for two group comparisons) or analysis of variance for means, for each of the six outcome measures: patient perception of shared decision making, ED visits, hospitalizations, controller medication use, beta agonist overuse, and use of oral steroids. Changes over time will be assessed using regression models, including the outcome measure as the dependent variable and study arm, time, and a study arm by time interaction term as independent variables to assess differences by intervention and whether changes over time vary by intervention. Analysis over time will employ generalized estimating equations to address correlation between measures at the same practice [24]. Analysis will be conducted using Statistical Analysis System (SAS) (version 9.3).

Principle investigators at each PBRN site will recruit and enroll clinics into the study. As well as explaining the study and randomization process, each site will provide potential practices with information on incentives for providers and practices such as continuing medical education (CME) category 1 credits for participation and up to 20 CME hours for satisfying MOC4 Metric Module for family medicine providers.

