For the purposes of the study, individual participants will be included in a cluster (clinic) by complete enumeration of patients with a diagnosis of asthma. Representatives from each clinic will agree to participate in the study prior to randomization. To ensure that randomization will be non-biased, randomization will occur centrally using a computer-generated algorithm run by the study statistician, who will not be involved in recruitment, data collection, or deployment of the intervention. Clinics will be randomized in groups by PBRN. Once each PBRN reaches its recruitment target, the list of clinics will be inputted into SAS and assignments to one of the three study arms will be generated randomly without replacement using the PROC PLAN procedure. Thereby, allocation to intervention or control group will be concealed from clinics and site PIs prior to full recruitment. Due to the nature of the intervention, which requires active clinic engagement, intervention assignment will be unblinded following randomization.

Sample size was determined using the method of Hayes and Bennett [25] for comparing proportions in clustered randomized trials. We computed the sample necessary to achieve minimum 80% power to test our primary hypothesis that the participatory dissemination strategy will experience greater improvements in patient outcomes compared to traditional dissemination and usual care. A sample size of 10 clinics, with a minimum of 50 patients per clinic, was determined based on preliminary data showing a 7-point decline in the proportion of patients with asthma exacerbation (i.e., ED visit or hospitalization) from 16% to 9% in clinics where the SDM Toolkit was implemented, and a coefficient of variation (*k*) equal to 0.06. To ensure adequate representation of asthma patients during the study period, we approached clinics with at least 75 asthma patients at baseline.

The outcome measure of asthma exacerbation resulting in an emergency department visit or inpatient admission will be determined using Medicaid claims data with the primary diagnosis of asthma (ICD-9 code 493) or a prescription for oral steroids. Misclassification may occur from coding errors but should be non-differential and not vary between the study’s arms since a single source of data will be used for all outcomes (Table 2). National surveillance studies [2] and intervention studies [7,26] have applied asthma ICD-9 codes to administrative data with useful interpretation of outcomes.

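### Clinics are randomised within four PBRNs, but the stated regression terms and bivariate tests leave PBRN out: a conditional loss of efficiency in between-arm comparisons of levels

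*Protocol article*

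**What the plan says.** The Abstract (Methods/design) states: "This non-blinded study will randomize 30 primary care clinics in NC stratified by four PBRNs". The Analysis section repeats that "Clinics will be randomized in groups by PBRN", using a separate computer-generated list for each network. The Setting section gives the stratum sizes: "two or three practices per arm for a total of six or nine practices per PBRN". With 30 clinics and equal allocation ("The first 30 consenting practices will be equally randomized into one of three study arms", Description of interventions), this means two networks of six and two of nine (6 + 6 + 9 + 9 = 30), and 10 clinics per arm.

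The Analysis section plans two kinds of comparison for six outcomes. The first is bivariate tests between arms: chi-square, t-test or ANOVA. The second is a regression with "study arm, time, and a study arm by time interaction term as independent variables". On correlation it says: "Analysis over time will employ generalized estimating equations to address correlation between measures at the same practice". PBRN appears in neither the regression terms nor the bivariate tests, and the sample-size method takes no credit for stratification.

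**The concern.** Balancing the arms within PBRN removes between-PBRN variation from the true sampling error of an arm difference. An analysis without PBRN still counts that variation in the estimated error. Where the networks differ in outcome, the estimated standard error of a between-arm level comparison is then too large: the test rejects too rarely under the null, intervals are too wide, and power is lost.

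The estimate itself is not biased, because the arms are balanced within each network. What is at stake is precision, with only 10 clinics per arm. The article gives some reason to expect differences. Its network table describes one network as rural and largely African-American and others as mixed urban and rural, and its Background reports threefold hospitalisation and ED rates in African-American children.

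**Working it through.** **Inputs from the article (Analysis).** p0 = 0.16 and p1 = 0.09 ("7-point decline in the proportion of patients with asthma exacerbation (i.e., ED visit or hospitalization) from 16% to 9" per cent); n = 50 patients per clinic (the stated minimum); 10 clinics per arm; k = 0.06; "minimum 80% power to test our primary hypothesis".

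**Assumptions.** Two-sided alpha 0.05 (not stated). The share or size of variation between PBRNs is not stated, so a range is shown. Bivariate tests are taken at clinic level, because the Abstract says outcomes are measured there.

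**1. Reproducing the plan's 10 clinics per arm.** Hayes–Bennett, unmatched:

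c = 1 + (z_α/2 + z_β)² × [p0(1−p0)/n + p1(1−p1)/n + k²(p0² + p1²)] / (p0 − p1)²

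- Binomial part: 0.002688 + 0.001638 = 0.004326.
- Between-clinic part: 0.0036 × (0.0256 + 0.0081) = 0.000121.
- c = 1 + 7.849 × 0.004447 / 0.0049 = 8.12, so 9 clinics suffice, and 10 give about 88% power.
- At alpha 0.025, for two comparisons, c = 9.63, which rounds up to 10 (power 81.8%).

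The stated 10 meets the target without any stratum term.

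**2. Loss if total between-clinic variation is k = 0.06.** Between-clinic variation is 0.000121 / 0.004447 = 2.7% of the variance of a clinic proportion. If all of it lay between PBRNs, the unadjusted standard error would be too large by √(0.004447 / 0.004326) = 1.014, i.e. 1.4%.

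| Test | Without PBRN | With PBRN |
|---|---|---|
| Normal approximation | 91.6% | 92.0% |
| t-test, 18 v 15 df | 89.2% | 88.2% |

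The 3 degrees of freedom cancel the gain. A simulation with total variation held at 0.06 gave 88.0% v 87.6%.

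**3. Loss if the PBRNs differ more than that.** With 3/3/2/2 clinics per arm, the within-arm variance picks up a fraction (10 − 26/10)/9 = 0.822 of the between-PBRN variance. Keep k = 0.06 within PBRN and add a between-PBRN CV:

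ratio of estimated to true SE = √[1 + 0.822 × CV² × 0.0337 / 0.004447]

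- CV 0.1: √(1 + 0.0623) = 1.031.
- CV 0.2: √(1 + 0.249) = 1.118. The 18-df critical value of 2.101 then acts like 2.101 × 1.118 = 2.35, a type I error of about 3%.

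Simulation of FLOW v control (4,000 to 5,000 trials per setting), clinic-level t-test v arm-plus-PBRN ANOVA:

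| Within-PBRN k | PBRN CV | Type I, without v with | Power, without v with |
|---|---|---|---|
| 0.10 | 0 | – | 87% v 86% |
| 0.06 | 0.2 | 3.0% v 5.0% | 83% v 87% |
| 0.10 | 0.2 | 3.2% v 5.1% | 82% v 86% |
| 0.10 | 0.3 | 1.9% v 4.9% | 74% v 86% |

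The value 0.10 for k is an assumption; the plan's figure is 0.06.

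**4. Is a CV of 0.2 plausible?** As an illustration, take the threefold rate from the Background, so that a network's rate is proportional to 1 + 2s, where s is the share of Black patients. Assumed shares of 25/35/35/65% give 1.5, 1.7, 1.7 and 2.3, with mean 1.8 and CV 0.17 to 0.19 (divisor 4 or 3). Shares of 30/35/35/50% give a CV of 0.09 to 0.10. So 0.2 is possible but at the upper edge of this illustration, and 0.3 is a sensitivity value only.

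**5. The arm-by-time term.** A constant PBRN difference cancels in within-clinic change. GEE was simulated (exchangeable, robust SE, 30 clinics, two periods, 400 runs) with total k = 0.25 and half the between-clinic variance between PBRNs. The interaction SE was 0.02858 with and without PBRN main effects. The SE of the arm difference at follow-up fell from 0.02472 to 0.02149.

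**6. The survey.** Table 2 collects it in arms 1 and 2 only, and no pre-intervention baseline is described, so comparing levels is the natural analysis. With an assumed 50% v 60%, 50 cards per clinic, k = 0.10 and a PBRN CV of 0.1, power is 56% without PBRN and 66% with it.

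**The case against.** The strongest reply is that the planned test of the clinical hypothesis is the arm-by-time term, for which PBRN main effects do nothing, and that on the plan's own k the loss is nil. Both points stand, and they confine the concern to level comparisons and to networks that differ by more than k = 0.06 allows. The reply does not dispose of the point. The same section plans bivariate level comparisons for all six outcomes and uses the regression to assess differences between arms as well as change.

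Second, the article introduces its terms with the word including, and an analysis plan that is not shown may add PBRN. That reading is open. Even so, the article does more than stay silent: it lists regressors and tests, and these do not follow the randomisation.

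Third, no outcome figure by PBRN is given, and networks may recruit outside their existing membership, which could blur differences. This stands, and is why the size is only conditional. Facilitator differences are not evidence for it either, since they act in the intervention arms and an additive PBRN term would not capture them.

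A reader might infer that the plan's tests are conservative in general and that the trial gives power away. The documents do not support this. In the GEE simulation, type I error for arm-by-time with robust SEs and normal critical values was about 6 to 11% (400 runs; Monte Carlo SE about 1 point), the opposite direction. That is a separate small-sample matter.

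**Conclusion.** The point holds in a limited form. The stated analysis does not use the groups by which clinics are randomised. Where outcomes differ between PBRNs, between-arm comparisons of levels lose precision. There is no bias, and the omission does not inflate type I error.

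The size depends on a quantity the article does not report. It is negligible if total between-clinic variation is k = 0.06. It is about 4 to 5 power points, with type I error near 3%, if the between-PBRN CV is 0.2, and larger only at values for which the article offers no support. The arm-by-time test is not materially affected unless time trends differ by PBRN. These figures assume two-sided 0.05, 50 patients per clinic and clinic-level tests. The change is worth making because it is nearly free, not because the stated power is shown to fail.

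**What to change.** Include PBRN (four levels, fixed effect) in every between-arm regression model. Replace the unstratified bivariate comparisons with clinic-level tests stratified by, or adjusted for, PBRN, the survey comparison of arms 1 and 2 included. If time trends are expected to differ by network, state whether a PBRN-by-time term is included, since main effects alone will not help the arm-by-time test.

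The cost is 3 degrees of freedom (18 to 15 in a two-arm clinic-level comparison) and one extra model term. If the PBRNs turn out not to differ, about 1 power point or less is lost (87% v 86% in the simulation at k = 0.10). Neither the design nor the sample size needs to change.

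### The sample size is for a plain comparison of two proportions, but improvement is assessed by an arm-by-time interaction that may have less than 80% power; a baseline-adjusted follow-up contrast should be named as primary

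*Protocol article*

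**What the plan says.** All of this is in the Analysis section of the protocol article, under Methods/design, unless noted.

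- **Sample size.** "Sample size was determined using the method of Hayes and Bennett [25] for comparing proportions in clustered randomized trials". The aim is to "achieve minimum 80% power to test our primary hypothesis", namely that "the participatory dissemination strategy will experience greater improvements in patient outcomes compared to traditional dissemination and usual care". The inputs are 16% and 9%, k = 0.06, 10 clinics and a minimum of 50 patients per clinic. No baseline term, change term or pre-post correlation is mentioned.
- **Clinic size.** As a margin, "we approached clinics with at least 75 asthma patients at baseline".
- **Analysis.** Two kinds are listed for the six outcomes. The first is bivariate comparison of the arms: chi-square for proportions, t-tests or analysis of variance for means. The second is regression on arm, time and arm by time, used "to assess differences by intervention and whether changes over time vary by intervention". Generalized estimating equations (GEE) for within-practice correlation are mentioned only for the second. Neither is called primary, and no baseline rate is listed as a covariate.
- **Data.** Table 2 gives quarterly Medicaid claims as the source for exacerbation outcomes in all three arms.

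**The concern.** The sample-size formula has one proportion per clinic, so a two-arm contrast carries two variances. If time runs from before to after randomisation, the arm term in the regression is the baseline difference and the interaction is the effect of dissemination. That is a difference of two changes, with four variances. For an uncommon binary event in clinics of 50 to 75 patients, the baseline proportion is itself noisy. Unless it correlates fairly strongly with follow-up, subtracting it adds more noise than it removes.

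Randomisation makes the arms equal at baseline in expectation, so a change contrast is not needed for validity. At stake is whether the test that allows for clustering has the power claimed for the improvement hypothesis. With 10 clinics per arm there is little room for loss.

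**Working it through.** **Inputs from the article:** p0 = 0.16, p1 = 0.09, k = 0.06, c = 10 clinics per arm, m = 50 (75 as a second case).

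**Assumptions:** two-sided alpha 0.05 (not stated in the article); one pre and one post period of equal length; 16% at baseline in both arms; pre-post correlation r of clinic proportions from 0 to 0.4.

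**1. The plan's own figure.** The variance of one clinic proportion is V(p) = p(1−p)/m + k²p². At m = 50:

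- V(0.16) = 0.002688 + 0.000092 = 0.002780
- V(0.09) = 0.001638 + 0.000029 = 0.001667
- Sum = 0.004447

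Clinics per arm = 1 + (1.96 + 0.84)² × 0.004447 / 0.07² = 1 + 7.85 × 0.004447 / 0.0049 = 8.12, so 9. With 10 clinics, power = Φ(√(9 × 0.0049 / 0.004447) − 1.96) = Φ(1.19) = 88%. The stated 10 clinics for at least 80% is therefore consistent with a follow-up comparison. Exactly 10 results from alpha 0.025 (9.63).

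**2. Arm-by-time contrast.** Variance = [2V(0.16)(1−r)] + [V(0.09) + V(0.16) − 2r√(V(0.09)V(0.16))]. At m = 50 this is 0.010008 − 2r × 0.004933.

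- r = 0: variance 0.010008; Φ(√(0.0441/0.010008) − 1.96) = Φ(0.14) = 56%
- r = 0.2: variance 0.008034; Φ(0.38) = 65%
- r = 0.4: variance 0.006061; Φ(0.74) = 77%

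For 80% power the variance must be at most 0.0441/7.85 = 0.00562, which needs r of about 0.44. The contrast matches the unadjusted follow-up comparison at r = (0.010008 − 0.004447)/(2 × 0.004933), about 0.56. At r = 0 it would need 1 + 7.85 × 0.010008/0.0049 = 17.03, so 18 clinics per arm.

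**3. Baseline-adjusted follow-up contrast.** Variance = 0.004447 × (1 − r²).

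| m | Contrast | r = 0 | r = 0.2 | r = 0.4 |
|---|---|---|---|---|
| 50 | Follow-up only | 88% | 88% | 88% |
| 50 | Arm by time | 56% | 65% | 77% |
| 50 | Baseline-adjusted | 88% | 90% | 93% |
| 75 | Follow-up only | 97% | 97% | 97% |
| 75 | Arm by time | 72% | 81% | 91% |
| 75 | Baseline-adjusted | 97% | 97% | 99% |

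At m = 75 the arm-by-time contrast reaches 80% at r of about 0.17.

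**4. Check by simulation.** This used clinic-level tests, 10 clinics per arm, m = 50, independent patients in the two periods and 4,000 runs. Power was 88% for follow-up only, 57% for change and 86% for baseline-adjusted. The last figure includes the degree of freedom spent on the covariate but none for PBRN.

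**5. Plausible r.** If different patients contribute to the two periods, k alone fixes r. In a control clinic it is 0.000092/0.002780 = 0.03, so a higher value has to come from the same patients appearing in both periods. The article gives no figure for that overlap.

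**The case against.** A reader might infer that the trial is underpowered, or that the stated 80% is wrong. The article does not support that, for four reasons.

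- **The interaction is not the only comparison planned.** The bivariate tests have the same form as the sample-size calculation, and nothing is named primary. This stands as far as it goes. However, the section assigns proportions to chi-square and describes no allowance for clustering there. The Abstract says outcomes are measured at clinic level, and a t-test on clinic proportions would match the calculation, but the text does not say that this is meant.
- **The loss depends on figures that are not given.** Fifty is the design minimum, and 75 at baseline is a floor for entry. Even at r = 0 the interaction reaches 80% at about 92 patients per clinic: (0.4851/92) + 0.0036 × 0.0849 = 0.00558, just under the 0.00562 needed. Overlap of patients would raise r. This stands.
- **Baseline length and the coding of time are not given.** Suppose the baseline is twice as long and its sampling variance is halved. At r = 0 and m = 50 the variance becomes 0.004447 + 2 × (0.001344 + 0.000092) = 0.007320, and power is 69%. The penalty is smaller but still present. If time covers only quarters after randomisation, the interaction is a contrast of slopes. The figures above would not apply, and the sample-size formula does not cover that contrast either.
- **An arm-by-time GEE is a standard and valid analysis, and covariate lists are often left to a SAP.** That is true. The point here is not an omitted covariate. The article itself fixes the model terms and attaches a power claim to the improvement hypothesis, and the two do not correspond.

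**Conclusion.** The mismatch between the sample-size formula and the model for improvement is real; the size of the loss is conditional. If the interaction is the primary test, with equal-length periods and two-sided alpha 0.05, power at 50 patients per clinic is about 56–77% for correlations of 0 to 0.4. It is below the stated minimum until about 0.44. At 75 patients it is about 72–91%, and below 80% only for correlations under about 0.17.

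The follow-up calculation has slack (88% with 10 clinics), so the stated 80% is not shown to be wrong. What can be said firmly is comparative. Apart from the degrees of freedom it uses, a baseline-adjusted follow-up contrast has at least as much power as either unadjusted contrast, and it stays above 80% at every correlation examined. It therefore removes the dependence on a correlation that the article does not give.

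**What to change.** Name one primary contrast: the follow-up exacerbation proportion by arm, in an analysis that allows for clustering and adjusts for the clinic's pre-randomisation proportion and for PBRN. A longitudinal model with a common baseline mean across arms would serve equally. Keep the arm-by-time interaction as a secondary description of trajectory. State the assumed pre-post correlation, the length of the baseline period and how time is coded.

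The cost is a change of wording, about one degree of freedom for the baseline covariate and three for the four PBRNs. With all 30 clinics in one model that leaves 30 − 3 − 1 − 3 = 23. Baseline-period claims must also be extracted, from the Medicaid source already planned in Table 2. No change to recruitment or to the interventions is needed.

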
**Table 2 Tab2:** **Measures for assessment of changes in patient asthma outcomes**

**Outcome**	**Data source**	**Study arms and networks**	**Collection frequency**
Patient perception of shared decision making [7]	Survey question “Who made the decision today?” collected via index cards at arm 1 and 2 practices	Arms 1, 2	Bimonthly
Asthma emergency department visits [27]	Medicaid claims, CHS Asthma Comparative Effectiveness Research Database	Arms 1, 2, 3	Quarterly
Asthma hospitalization rate [27]	Medicaid claims, CHS Asthma Comparative Effectiveness Research Database	Arms 1, 2, 3	Quarterly
Controller medication use	Medicaid claims	Arms 1, 2, 3	Quarterly
Beta agonist overuse [28]	Medicaid claims	Arms 1, 2, 3	Quarterly
Exacerbation requiring oral steroid [27]	Medicaid claims, CHS Asthma Comparative Effectiveness Research Database	Arms 1, 2, 3	Quarterly

Data was obtained from surveys, insurance claims, and research databases.

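### With only 10 clinics per arm, the planned GEE should state a small-sample correction: uncorrected Wald tests would reject a true null about 7–13% of the time, not 5%

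*Protocol article*

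**What the plan says.** In the Protocol article, the Analysis section assesses change over time by regression with "study arm, time, and a study arm by time interaction term as independent variables to assess differences by intervention". It continues: "Analysis over time will employ generalized estimating equations to address correlation between measures at the same practice". This is the only adjustment for clustering that the analysis text names; the bivariate comparisons listed just before it are chi-square tests, t-tests and analysis of variance. The section gives the software and its version. It does not name a variance estimator, a working correlation, a Wald or score test, a reference distribution or an alpha level.

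The number of clusters is fixed elsewhere. Description of interventions says: "The first 30 consenting practices will be equally randomized into one of three study arms". That gives 10 clinics per arm. Table 2 says the shared-decision survey is "collected via index cards at arm 1 and 2 practices", so that outcome has 20 clinics in total.

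**The concern.** The usual GEE variance (the empirical sandwich) is justified when the number of independent clusters is large. With 10 clinics per arm two things go wrong, both in the same direction. The fitted model absorbs part of each clinic's deviation, so the residuals that feed the sandwich are too small. A normal or chi-square reference then treats that variance as known, although it is estimated from very few clinics. More patients or more quarters do not help, because neither adds clinics. The same holds whether the data rows are patients or clinic-by-quarter summaries.

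The arm and arm-by-time terms carry the comparison of FLOW with traditional dissemination and with control. Anti-conservative tests of those terms could credit FLOW with an effect that it does not have, and nominal 95% intervals would cover less than 95%.

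**Working it through.** **Inputs from the Protocol article.** 30 clinics allocated equally to three arms, so c = 10 per arm (Description of interventions); 20 clinics for the survey (Table 2); quarterly claims outcomes (Table 2); arm, time and arm-by-time terms (Analysis).

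**Assumptions, not in the article.** Two-sided alpha 0.05; 8 quarters; quarterly event probability 4%; mean clinic size 60; clinic-size CV 0 or 0.6; between-clinic SD 0.06 or 0.25 on the logit scale for level and slope; time entered as linear.

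**Step 1. The plan's own figure.** The article states "We computed the sample necessary to achieve minimum 80% power to test our primary hypothesis" and "A sample size of 10 clinics, with a minimum of 50 patients per clinic, was determined based on preliminary data", with a fall "from 16% to 9% in clinics where the SDM Toolkit was implemented" and k = 0.06. The Hayes-Bennett formula is

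c = 1 + (z_α/2 + z_β)² × [p0(1−p0)/m + p1(1−p1)/m + k²(p0² + p1²)] / (p0 − p1)²

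With p0 = 0.16, p1 = 0.09, m = 50 and k = 0.06:
- bracket = 0.002688 + 0.001638 + 0.000121 = 0.004447
- (1.960 + 0.842)² = 7.849
- c = 1 + 7.849 × 0.004447 / 0.0049 = 8.12, so 9 clinics per arm.

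Ten clinics give about 88% power: 0.07 × √(9/0.004447) − 1.960 = 1.19, and Φ(1.19) = 0.88. With alpha 0.025 (an assumption, for two comparisons) c = 9.63, so 10. The stated 10, read as per arm, is consistent with at least 80% power.

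**Step 2. Closed form, 10 against 10 clinics.** With equal clinic sizes and roughly normal clinic summaries of equal variance, the uncorrected sandwich gives (c−1)/c = 0.9 times the unbiased variance of the arm difference. The Wald test therefore rejects when |t| > 1.96 × √0.9 = 1.859, where t has 2(c−1) = 18 degrees of freedom.

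Type I error = 2 × P(t18 > 1.859) = 7.9%.

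This needs no event rate or number of quarters, so it bears on the survey as well as on the claims outcomes. A simulation of 400,000 null draws also gave 7.9%. With the unbiased variance and a t18 reference it gave 5.0%. The uncorrected three-arm 2-df Wald test on such summaries gave 10.2%.

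**Step 3. Logistic GEE simulation under no effect.** Independence working correlation, clinic as cluster, 2,500 runs per scenario (Monte Carlo SE about 0.5–0.7 points), test of the arm-by-time term. Ranges run over the two between-clinic SDs and, where not separated, the two size CVs.

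| Design and test | Uncorrected robust Wald | Robust score | Mancl-DeRouen with t |
|---|---|---|---|
| 20 clinics, equal sizes | 7.4% | 4.9% | 3.9% |
| 20 clinics, size CV 0.6 | 8.8–9.1% | 5.4% | 4.1% |
| 30 clinics, one pairwise contrast | 8.4–9.8% | not run | 4.5–5.2% |
| 30 clinics, joint 2 df | 10.0–13.0% | 4.1–4.6% | not run |

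**Step 4. Cost in precision.** In the equal-size 10 against 10 case, the corrected half-width relative to the uncorrected one is (t18 / z) × √(10/9) = (2.101 / 1.960) × 1.054 = 1.13, so about 13% wider.

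**The case against.** The strongest objection is that the article never states the analysis that fails. It commits to GEE and is silent on variance, test and reference distribution. A condensed article commonly leaves such details to the full protocol or the analysis plan, neither of which is shown. GEE clustered on the randomized unit is a valid choice and does not exclude a correction. The result also depends on the test: an uncorrected robust score test stayed close to 5% in the simulation.

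Most of this stands. A reader might infer that the trial's longitudinal tests do run at an inflated level; the article does not support that, because it does not say that uncorrected Wald inference will be used. Two further inferences also fail:
- That a joint test of many quarter-by-arm terms will inflate the error far more. The article describes time and one arm-by-time term, and quarterly is a collection frequency, not a statement that time is categorical.
- That the trial clinics run from solo practices to large health centers. The Setting section says this of the whole consortium. Trial clinics need at least 75 eligible Medicaid asthma patients, and their size distribution is not given.

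What the objection does not remove is the pairing that the article itself fixes: GEE as the named remedy for clustering, and 10 clinics per arm. Run in its ordinary form, that pairing is anti-conservative even with equal clinic sizes. A score test would protect the p-value, but the article does not choose one, and it would leave Wald intervals for the arm effects too narrow. The sample-size formula includes an added clinic as an allowance for few clusters; the analysis text shows no counterpart.

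**Conclusion.** The point holds as a conditional one. If the planned GEE is run with an uncorrected sandwich variance and Wald tests, a nominal two-sided 5% test would have a type I error of about 7–10% for pairwise contrasts and about 10–13% for the three-arm 2-df test. The 7.9% figure for 10 against 10 rests only on equal clinic sizes and approximately normal clinic summaries of equal variance. The wider ranges rest on the assumed 8 quarters, 4% quarterly event rate, size CV of 0 to 0.6 and between-clinic SD of 0.06 to 0.25. Nothing in the Analysis section is false, and GEE is usable with this number of clinics once corrected. This is an inexpensive improvement to the stated method and does not show that the planned tests are invalid.

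**What to change.** In the Analysis section, specify GEE with clinic as the cluster, a small-sample-corrected sandwich variance (for example Mancl-DeRouen or Kauermann-Carroll), and a t reference for pairwise contrasts or an F reference for the three-arm test, with degrees of freedom based on the number of clinics. Take the confidence intervals from the same corrected variance. A clinic-level analysis, or a permutation test that follows the randomization within PBRN, is an acceptable alternative. If the analysis plan already fixes one of these, a cross-reference is enough.

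The cost is a sentence or two and a software option, after checking that the chosen procedure offers the correction. Intervals become somewhat wider, about 13% in the equal-size case above. Mancl-DeRouen with t was slightly conservative with 20 clinics (3.9–4.1%). On the article's own inputs, 10 clinics per arm give about 88% power at two-sided 5%, by a formula that already allows for few clusters, so the change fits the stated design. If alpha were split to 0.025, 10 clinics would be just enough.
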